**Figure 1 figure1:**
[figure not shown]
Screenshot of the web page for survivors of lung cancer and their close contacts. LC: lung cancer.

Patients interested can consent and enroll through this study’s website using digital or paper forms. Participants are invited to provide contact information (email or phone number) for the close ones they wish to refer for inclusion in the second cohort of our study. They are also advised to inform their close contacts that they shared their details with the research team and that their informed consent will be mandatory before participation.

#### Cohort 2

The second cohort includes participants being referred for inclusion into our study by the participants of cohort 1. Referred participants should be aged older than 18 years. Individuals with a personal history of LC are excluded. Referred participants are contacted by our research team through emails, phone calls, or through a recruitment pamphlet mailed for those without internet access. Participants are encouraged to access our study’s website [19]. The web page section directed at cohort 2 (Figure 1B) provides general information on LC, its epidemiology, information on LC screening programs and the risk-based eligibility, and information on risk mitigation strategies such as smoking cessation and home radon testing. The enrollment of referred participants is also carried out with a submittable digital form available on this study’s website. Participants lacking the digital literacy to enroll by themselves are contacted by the research team to enroll over the phone or through mailed material.

Once enrolled, participants have their 6-year risk of LC estimated with the PLCOm2012 (Prostate, Lung, Colorectal and Ovarian Cancer Screening Trial) risk model [20]. The risk prediction PLCOm2012 model has been extensively validated in previous studies [21,22]. The PLCOm2012 model has also shown adequate properties to discriminate patients with LC in a large cohort of Quebec smokers [23]. Moreover, data from the International Lung Screening Trial have shown that the PLCOm2012 model was more efficient compared to the US Preventative Services Task Force 2013 criteria to identify high-risk individuals to enroll into LC screening programs [24]. Participants who meet the eligibility criteria for the provincial LC screening program (ie, aged between 55 and 74 years and PLCOm2012 score ≥2%) are directed toward the provincial LC screening program to complete LDCT.

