For referred participants (cohort 2), the web-based questionnaire collects their known personal history of chronic obstructive pulmonary disease, prior exposure to radon or asbestos, smoking habits, and nicotine dependence using the Fagerström Tolerance questionnaire [33]. Data are used to calculate their PLCOm2012 six-year LC risk. The perceived risk of developing LC is assessed by asking “Compared with others your age, what do you think your chances are of being diagnosed with LC during your lifetime?” rated on a 5-point Likert scale. We also assess whether referred participants believe their risk is high or low due to genetics or smoking exposure and which they think is more important in increasing their lifetime LC risk. Generalized anxiety is assessed at baseline using the General Anxiety Disorder 7-item questionnaire (GAD-7) [34], and a question asks if they believe their anxiety is associated with their perceived risk of LC. We repeat the GAD-7 at 28 days after enrollment to assess the impact of the LC screening risk assessment on anxiety levels. Patients will be asked to give their consent to access their provincial health records within the 18 months following their enrollment in this study. Extracted data will consist of whether these participants underwent LC screening via LDCT within 18 months after enrollment. No data about the results of the LDCT imaging will be extracted.

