### Statistical Analysis

#### Quantitative Analysis

Participants with LC who refer at least one peer for participation will be compared to those who did not refer a peer for participation. To identify the predictive factors of referral, multivariable logistic regression will be used, adjusting for age, sex, educational attainment, health literacy, PAM score, and phase of LC trajectory. The dependent variable in the logistic regression will be referral by patients with LC. Using logistic regression, we will also examine if increased patient with LC activation is associated with increased odds of referral. Chi-square tests and 2-tailed *t* tests will be used for comparisons of categorical and continuous variables.

Referred participants who are eligible for LC screening will be considered as cases. A control group will be selected from patients who were either self-referred or referred by their primary care physician to the Quebec LC screening program and matched by age (1:1). To determine if participants in cohort 2 have a higher risk of LC than the controls, the mean PLCOm2012 scores will be compared using 2-tailed *t* tests in our cohort and in the Quebec LC screening program. The predictive factors of being eligible for LC screening and whether being referred by survivors of LC is associated with increased odds of being eligible will be examined using multivariable logistic regression. We will account for clustering among individuals referred by the same family member using a random effect model.

Spearman coefficients will be calculated to assess the correlations between the actual risk and the perceived risk of LC. Kruskal-Wallis tests will be used to compare actual and perceived risks of LC with different levels of anxiety. Odds ratios and their 95% CIs will be reported. All statistical analyses will be conducted using R (version 4.2.0; R Foundation for Statistical Computing).

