## Results

Enrollment in the cohorts was conducted from June 2023 to January 2024, with participants being followed up through July 2025. Overall, we have enrolled 25 survivors of LC who have referred 84 of their close contacts to this study. The results of this study are expected to be reported at the end of 2025 through publications in peer-reviewed journals and presentations at relevant national and international conferences.

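### Perceived risk is asked relative to age peers over a lifetime but correlated with an absolute six-year score, so the unadjusted Spearman coefficient may be attenuated by age and a low value could not be read as misperception

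*Protocol article*

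**What the plan says.** Data Collection, Cohort 2, gives the perceived-risk item as "Compared with others your age, what do you think your chances are of being diagnosed with LC during your lifetime". The answer has five ordered categories, being "rated on a 5-point Likert scale". The same section says of the questionnaire answers: "Data are used to calculate their PLCOm2012 six-year LC risk". Participants Eligibility and Recruitment, Cohort 2, uses that score as an absolute percentage: the provincial programme takes people "aged between 55 and 74 years and PLCOm2012 score ≥2" percent.

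Statistical Analysis, Quantitative Analysis, then states: "Spearman coefficients will be calculated to assess the correlations between the actual risk and the perceived risk of LC". It names no age adjustment, age-specific ranking or conversion to a lifetime horizon for this correlation. It does not define actual risk, but PLCOm2012 is the only risk that the study calculates. The section on focus groups also ties clinical risk to PLCOm2012 scores.

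The age range of cohort 2 is wide by rule: "Referred participants should be aged older than 18 years", with no upper limit. The 55 to 74 band applies to programme eligibility, not to entry into the cohort.

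**The concern.** The two measures differ in two ways. The item is relative to people of the same age, while the score is absolute. The item covers a lifetime, while the score covers six years.

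The first difference matters for a rank correlation in a cohort of mixed ages. Suppose the score rises with age. A young heavy smoker may rightly answer that the risk is well above that of age peers and still have a low six-year score. An older person with an average history may rightly answer that the risk is about the same as that of peers and have a higher score. Both answers are correct, yet the pair counts against the correlation.

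The planned coefficient then mixes two things: how well participants judge their risk, and how much of the spread in the score is due to age. A low value could be reported as relatives misjudging their risk when part of the shortfall comes from the scales. The Discussion treats perceived risk as a motivator for screening and cites a positive correlation with estimated risk in another cohort, so such a misreading could carry a practical message.

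**Working it through.** **The plan's own figure.** The protocol states no expected value, sample size or power for this correlation. The 194 under Sample Size concerns a comparison of proportions. It reproduces at 97 per group for 40% against 60% (two-sided 5%, 80% power) and has no bearing here.

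**Inputs from the protocol.** Item relative to age peers, lifetime, five categories; score absolute, six-year; cohort open to everyone over 18; Spearman coefficient with no age term.

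**Inputs assumed, because the protocol does not give them.** Slope b of log risk on age: 0.05 to 0.10 per year. Standard deviation s of log risk from everything other than age: 0.8 to 2.0. Ages uniform over a stated range and independent of non-age risk.

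**Model.** Log risk = b × age + r, with r normal, mean 0 and standard deviation s. A perfectly accurate respondent to the item as worded reports the fifth of r in which he or she falls. Spearman uses ranks only, so it makes no difference that the score is a percentage and the model is on the log scale.

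**By hand, one central case.** For ages uniform over a range of width R, the variance due to age is b²R²/12. With b = 0.08, s = 1.0 and ages 20 to 80:
- Age variance = 0.0064 × 3600/12 = 1.92.
- Age share of the total = 1.92/(1.92 + 1.00) = 0.66.
- Pearson correlation of r with log risk = √(1.00/2.92) = 0.585.

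Simulating the same case with five answer categories gives a Spearman coefficient of 0.53. For ages 55 to 74 the age variance is 0.0064 × 361/12 = 0.19, the Pearson correlation is √(1.00/1.19) = 0.92, and the simulated Spearman coefficient is 0.88.

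**Simulation over the assumed ranges** (200,000 participants per scenario, every answer perfectly accurate; b from 0.05 to 0.10):

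| Ages | s = 0.8 to 1.2 | s = 2.0 |
|---|---|---|
| 20 to 80 | 0.37 to 0.77 | 0.71 to 0.89 |
| 30 to 80 | 0.43 to 0.82 | 0.77 to 0.91 |
| 55 to 74 | 0.78 to 0.95 | 0.94 to 0.97 |

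**Comparators in the same data.** A perfectly accurate five-category answer to an absolute question on the score's own horizon gives 0.98 in every scenario. The five-point scale therefore costs only about 0.02, and the rest of the loss is due to age. The Spearman coefficient of the item as worded, partial on age, is 0.92 to 0.98.

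**Sensitivity to the assumptions.** With bell-shaped ages (mean 58, SD 13) and s of 0.8 to 1.2, the unadjusted coefficient is 0.50 to 0.86. If age and non-age risk are correlated at −0.3 or +0.3, the value for ages 20 to 80, b = 0.08 and s = 1.2 moves from 0.60 to 0.46 or 0.73.

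**Not modelled.** The lifetime versus six-year difference. No figure above includes it.

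**The case against.** The strongest reply is that the size is not known. The protocol gives neither the age effect in PLCOm2012, nor the spread of non-age risk, nor the ages of the 84 referred contacts. It sets an age floor, which is not an age distribution. The Limitations section says only that first-degree relatives may be over-represented. The cohort has no smoking criterion, so non-age risk could vary widely, and at s = 2.0 the loss is much smaller. This stands: the mismatch is certain, its numerical effect is not.

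The near-perfect partial coefficient is also partly built in. The simulated answer is defined as the non-age part, and the partial coefficient removes the age part. This too stands. The partial coefficient addresses the age mismatch only; it does nothing for the horizon.

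The correlation is in neither the primary nor the secondary list of Table 1. The listed outcome on barriers and facilitators comes from focus groups and is analysed qualitatively. So this coefficient decides no listed outcome.

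It can also be said that an article leaves such detail to an analysis plan. That does not dispose of the point. The article states both the item wording and the coefficient, and the same section names age where it adjusts the referral model and matches controls.

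A reader might infer more than the documents support:
- **That accurate participants are bound to look poorly calibrated.** Spearman measures rank association, not calibration. The protocol promises only correlations, and several scenarios above leave the coefficient high.
- **That the anxiety analysis has the same fault.** The plan says "Kruskal-Wallis tests will be used to compare actual and perceived risks of LC with different levels of anxiety", which is most naturally read as comparing each risk across anxiety levels separately. Then no mismatch arises, and whether absolute risk relates to anxiety is a fair question in its own right.

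**Conclusion.** The point holds as a limit on interpretation. The plan correlates a lifetime rating relative to age peers with an absolute six-year score, in a cohort open to all adults, and states no alignment. If the score rises with age, the unadjusted coefficient may be attenuated even when participants judge their age-relative risk accurately, so a low value could not be read as misperception.

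Under the stated assumptions, the ceiling for perfect answers is about 0.37 to 0.89 for ages 20 to 80, against 0.98 for a matched question. The loss is small to moderate within ages 55 to 74, where the ceiling is about 0.78 to 0.97. These are illustrations, not estimates for this cohort. Importance is limited because the analysis is exploratory and not a listed outcome.

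**What to change.** In Quantitative Analysis, make the Spearman correlation of perceived risk with PLCOm2012, partial on age, the main coefficient. Ranking PLCOm2012 within age bands is an acceptable alternative. Report the unadjusted coefficient as descriptive. Describe the result as agreement on risk relative to age peers. State that the item asks about a lifetime and the score about six years, and that age adjustment does not remove this difference. Leave the Kruskal-Wallis comparisons with anxiety as they are.

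The Results section reports that enrolment has ended ("we have enrolled 25 survivors of LC who have referred 84 of their close contacts to this study"), so rewording the item is no longer a practical remedy, but the analysis can still be changed. Age is among the baseline data, so nothing new is collected. The cost is a short change of wording and one more coefficient in an exploratory analysis.

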#### Both Cohorts

Focus groups are conducted to explore the perceptions of LC risk (perceptions of genetic risk based on polygenic scores vs perceptions of clinical risk based on PLCOm2012 scores) and their associations with engagement in LC screening and preventative behaviors (such as smoking cessation, radon measurement, and remediation). Qualitative questionnaires and clinical scenarios are presented to this study’s participants of both cohorts to explore these themes and elucidate the most prevalent barriers and facilitators toward engagement in preventative behaviors and screening programs. Focus groups will be audio visually recorded and transcribed in verbatims.

### Statistical Analysis

#### Quantitative Analysis

Participants with LC who refer at least one peer for participation will be compared to those who did not refer a peer for participation. To identify the predictive factors of referral, multivariable logistic regression will be used, adjusting for age, sex, educational attainment, health literacy, PAM score, and phase of LC trajectory. The dependent variable in the logistic regression will be referral by patients with LC. Using logistic regression, we will also examine if increased patient with LC activation is associated with increased odds of referral. Chi-square tests and 2-tailed *t* tests will be used for comparisons of categorical and continuous variables.

Referred participants who are eligible for LC screening will be considered as cases. A control group will be selected from patients who were either self-referred or referred by their primary care physician to the Quebec LC screening program and matched by age (1:1). To determine if participants in cohort 2 have a higher risk of LC than the controls, the mean PLCOm2012 scores will be compared using 2-tailed *t* tests in our cohort and in the Quebec LC screening program. The predictive factors of being eligible for LC screening and whether being referred by survivors of LC is associated with increased odds of being eligible will be examined using multivariable logistic regression. We will account for clustering among individuals referred by the same family member using a random effect model.

Spearman coefficients will be calculated to assess the correlations between the actual risk and the perceived risk of LC. Kruskal-Wallis tests will be used to compare actual and perceived risks of LC with different levels of anxiety. Odds ratios and their 95% CIs will be reported. All statistical analyses will be conducted using R (version 4.2.0; R Foundation for Statistical Computing).

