**Primary outcomes**			
	Number of referred participants per individuals with LC^a^ (survivors of LC)	Questionnaire: cohort 1	
	Mean risk of LC in the referred population	Questionnaire: cohort 2 PLCOm2012 model	

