### Data Collection

#### Overview

Data are collected using the REDCap (Research Electronic Data Capture; Vanderbilt University) platform [28]. Participants are sent links to complete the web-based questionnaires.

Baseline data collected for all participants include sociodemographic characteristics (age, sex, education level, and ethnicity), health literacy, and smoking status. Health literacy is assessed with the 3-item Brief Health Literacy Screen [29] questions: “How often do you have someone help you read hospital materials?” “How confident are you filling out medical forms by yourself?” and “How often do you have problems learning about your condition because of difficulty understanding written information?” rated on 5-point Likert scales.

#### Cohort 1

For participants with LC (cohort 1), the phase of LC trajectory (investigative, treatment, or surveillance), tumor stage, performance status (as defined per Eastern Cooperative Oncology Group performance status grading), and their relationship to the referred participants are collected. The degree of self-empowerment they experienced by referring peers and family members for LC screening is assessed using the 13-item Patient Activation Measure (PAM) questionnaire [30]. The 13-item PAM questionnaire is a validated instrument to measure patient knowledge, skills, beliefs, and confidence for self-managing health. Patient activation stands as an important pillar of patient-centered care [31], and evidence has shown that being engaged and active in one’s own care is linked to better outcomes [32]. For each participant with LC, the number of unique web page visits is quantified using Google Analytics, and the number of referrals per participant with LC is collected. For participants who refer family members only, supplementary questions are asked to explore the potential barriers: “I don’t feel comfortable speaking with friends or close contacts about their health”; “I did not want my friends or close contact who smoke or used to smoke feel judged about their smoking”; “I did not want my friends to worry about their risk of LC”; “Speaking about LC screening and/or LC in general brings up negative emotions for me”; “I don’t see or speak with my friends or close contacts very often”; and “This study did not help me feel more comfortable discussing the potential benefits of LC screening.”

#### Cohort 2

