### Sample Size

Preliminary data from the provincial LC screening program indicate that 40% of patients either referred to the program by their primary care physician or via self-referral meet the eligibility criteria for LC screening. The McGill University Health Centre receives approximately 800 new patients with LC annually, and the provincial LC screening program receives around 100 referrals each month. With a sample size of 194 referred participants, we will be able to detect a 20% difference in the rates of referral, with a power of 80% and an α value of .05.

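### The yes/no referral model in cohort 1 puts at least 7 slopes on a closed cohort of 25 survivors, so its odds ratios will be unestimable or badly overfitted

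*Protocol article*

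**What the plan says.** Under Quantitative Analysis, the protocol article sets the comparison: "Participants with LC who refer at least one peer for participation will be compared to those who did not refer a peer for participation". It then names the method and the covariates: "multivariable logistic regression will be used, adjusting for age, sex, educational attainment, health literacy, PAM score, and phase of LC trajectory". The outcome is fixed as well: "The dependent variable in the logistic regression will be referral by patients with LC". A further sentence says that logistic regression will also be used to ask whether higher activation goes with higher odds of referral; it names no covariates.

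The Data Collection section gives three levels for one covariate: "the phase of LC trajectory (investigative, treatment, or surveillance".

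The Results section reports that "Enrollment in the cohorts was conducted from June 2023 to January 2024", and then: "Overall, we have enrolled 25 survivors of LC who have referred 84 of their close contacts to this study". So 25 is the final size of cohort 1, not an interim count.

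The first primary outcome in Table 1 is a count: "Number of referred participants per individuals with LC". The Sample Size section justifies 194 referred participants. It gives no size for cohort 1.

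**The concern.** A logistic model draws its information from the smaller outcome group. With 25 people that group is small at any split, and the covariate list is long for it. Two failures are possible. The first is separation: some combination of covariates predicts referral perfectly, at least one odds ratio goes to zero or infinity, and the software returns a meaningless estimate or a warning. The second is overfitting: the fit converges, but the coefficients are pushed away from the null and the intervals are too wide to use.

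The article commits to reporting odds ratios with 95% confidence intervals. Those from this model are the planned evidence on which patient characteristics predict referral, and possibly on the role of activation. A reader could take an inflated PAM odds ratio as support for the claim that activated patients refer more.

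**Working it through.** **1. The plan's own sample size.** The Sample Size section starts from a rate at which "40% of patients either referred to the program by their primary care physician or via self-referral meet the eligibility criteria for LC screening". Reading the 20% difference as 40% versus 60%, two-sided 5% (sidedness is not stated), 80% power, 1:1, without continuity correction:

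n per group = [1.96·√(2·0.5·0.5) + 0.8416·√(0.4·0.6 + 0.6·0.4)]² / 0.20² = (1.386 + 0.583)² / 0.04 ≈ 96.9, rounded up to 97; total 2 × 97 = 194.

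The stated figure reproduces. It starts from eligibility among people referred to the program and counts referred participants, so it gives no support to the cohort 1 model.

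**2. Parameters.** Age 1, sex 1, education at least 1, health literacy at least 1, PAM 1, phase 3 − 1 = 2. Sum: at least 7 slopes, or 8 coefficients with the intercept. Finer coding of education or health literacy would add more.

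**3. Events per slope and separation.** Events are the smaller outcome group. The article does not give the number of non-referrers, so it is varied here as an assumption. Separation was simulated with n = 25, seven slopes and null effects; the range reflects different phase splits.

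| Non-referrers of 25 | Events per slope | Simulated separation |
|---|---|---|
| 12 (best case) | 12/7 = 1.7 | about 6–45% |
| 5 | 5/7 = 0.7 | 49–69% |
| 3 | 3/7 = 0.4 | 92–95% |
| 0 | none | outcome constant, no fit |

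The ranges cover the splits tried and are not limits. A phase with a single patient, for example, always causes quasi-complete separation, because everyone in it has the same outcome.

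The average is 84/25 = 3.36 contacts per survivor. This suggests few non-referrers but does not prove it, since a few survivors could account for most referrals.

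**4. Fits that do not separate.** A second simulation (500 datasets per setting, phases split 20/40/40) gave PAM a true log odds ratio of 0.7 per SD, an odds ratio of e^0.7 = 2.0.

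| n | Referring (nominal) | Median estimated log OR | Upper/lower ratio of the 95% CI |
|---|---|---|---|
| 25 | 50% | 1.04 | 19.0 |
| 25 | 60% | 1.16 | 23.9 |
| 25 | 70% | 1.10 | 24.6 |
| 25 | 80% | 1.12 | 38.2 |
| 25 | 90% | 0.84 | 32.8 |
| 140 | 50% | 0.75 | 2.3 |
| 140 | 80% | 0.75 | 2.6 |

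At 50–80% referring, a true odds ratio of 2.0 shows up as about e^1.04 = 2.8 to e^1.16 = 3.2. At 50%, a ratio of 19 around 2.83 means an interval of about 2.83/√19 = 0.65 to 2.83·√19 = 12.3. The same model is well behaved at n = 140, so the size of the cohort is the cause.

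**5. Chi-square tests.** The smallest of three phase groups has at most 8 of 25 people. Even with 12 non-referrers, its expected count of non-referrers is at most 12·8/25 = 3.84, always below 5. For a two-level covariate split 12/13, the smallest expected count is 12·12/25 = 5.76 with 12 non-referrers and 10·12/25 = 4.8 with 10.

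**The case against.** The best reply is that this is a self-described pilot, that the referral model supports none of the listed primary or secondary outcomes, and that the article names no estimator, so a penalised fit may be specified in an analysis plan not shown here. This limits the importance of the point. It does not remove it: the article itself fixes the outcome and the covariate list, and seven slopes are too many for 25 people under any estimator.

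Several stronger readings are tempting, and the documents do not support them.

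- *The model will probably separate.* This depends on the unreported number of non-referrers. Near an even split, separation is the less likely result. Only the statement that the model will separate or overfit holds across the range.
- *The plan discards its primary outcome.* The count per survivor is still collected and can be summarised; only this regression reduces it to yes/no. A yes/no outcome is also a natural answer to whether patients are willing to refer.
- *The first objective rests entirely on this model.* Willingness can be answered by the count and the proportion referring. The separate sentence on activation could mean a PAM-only model.
- *Survivors who referred only relatives count as non-referrers.* The word used for the comparison groups is loose, but the dependent variable is defined as referral by patients with LC, without that limit.
- *All chi-square tests are invalid.* That is certain only for the three-level phase.

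**Conclusion.** The point stands for the adjusted yes/no model and should be fixed, though no listed primary or secondary outcome depends on it. With 25 survivors and at least 7 slopes, events per slope cannot exceed 1.7. Whether the result is separation or overfitting depends on the number of non-referrers, which the article does not give. If the Results sentence means that all 25 referred someone, the model cannot be fitted.

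The ceiling of 1.7 needs no assumption beyond the article's own numbers and one slope each for education and health literacy. The separation probabilities and the inflation figures rest on simulated covariates and assumed phase splits, and should be read as orders of magnitude.

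**What to change.** Change the Quantitative Analysis text for cohort 1 as follows.

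1. Limit the yes/no model to PAM plus at most one prespecified covariate, and fit it by Firth-penalised logistic regression. Say that it will not be fitted if every survivor referred someone.
2. Use Fisher's exact test in place of chi-square wherever an expected count is below 5, which includes every comparison by phase.
3. Relate PAM to the number of contacts referred per survivor, keeping zeros and counting both family and friends, with a quasi-Poisson or negative binomial model. This count is already a primary outcome, and it can still vary if nearly everyone referred.
4. State that a referral means any family member or other close contact.
5. Label these analyses exploratory.

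The cost is a change of wording, with no new data. The plan loses adjustment for most of the listed covariates, and the findings on who refers carry an exploratory label. The change should be recorded before the cohort 1 data are analysed, or else reported as a departure from the published protocol.

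### The case definition conflicts with the analyses it feeds: the eligibility odds ratio cannot be estimated, and the comparison of mean risk is biased if it uses the same cases

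*Protocol article*

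**What the plan says.** All statements are from the protocol article.

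- **Cases** (Quantitative Analysis): "Referred participants who are eligible for LC screening will be considered as cases". The Cohort 2 section sets eligibility at age 55 to 74 and a PLCOm2012 score of at least 2%.
- **Controls** (Quantitative Analysis): "A control group will be selected from patients who were either self-referred or referred by their primary care physician to the Quebec LC screening program", "matched by age (1:1"). Eligibility is neither required nor excluded.
- **Mean-risk comparison** (Quantitative Analysis): a two-tailed t test on mean PLCOm2012 score. This sentence names the participants of cohort 2, not the cases.
- **Eligibility model** (Quantitative Analysis): multivariable logistic regression will examine "whether being referred by survivors of LC is associated with increased odds of being eligible".
- **Primary outcome** (Table 1): "Mean risk of LC in the referred population". The abstract likewise compares scores of referred participants with program controls and sets no eligibility condition.
- **Sample Size**: "40% of patients either referred to the program by their primary care physician or via self-referral meet the eligibility criteria for LC screening". The planned number is 194, for a 20% difference with 80% power and alpha .05.

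**The concern.** Objective 2 asks whether survivor referral engages higher-risk people than usual care does. Two analyses serve it: a t test on the risk score and a logistic model of eligibility. The stated case definition selects people on the score that the t test compares and on the outcome that the model predicts. Other sentences describe an analysis without that selection. An analyst who follows the definition gets a model that cannot be fitted and possibly a biased t test. An analyst who follows the other sentences leaves the definition unused. The plan does not settle which to do.

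**Working it through.** **1. The plan's own sample size.** Take 40% against 60%, two-sided alpha .05, 80% power and pooled variance:

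n per group = [1.960 × √(2 × 0.5 × 0.5) + 0.842 × √(0.40 × 0.60 + 0.60 × 0.40)]² / 0.20² = 96.9, so 97 per group and 194 in total.

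The figure of 194 is reproduced as the total of two groups, although the text attaches it to referred participants. The calculation compares eligibility proportions, so it needs ineligible referred people in the analysis. The case definition removes them.

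**2. The eligibility model.** No assumption about the score distribution is needed. If 40% of the 84 referred people are eligible, there are 0.40 × 84 = 33.6, or about 34 cases. With 34 controls, 40% of them eligible:

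| | Eligible | Not eligible |
|---|---|---|
| Cases | 34 | 0 |
| Controls | 13.6 | 20.4 |

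Odds ratio = (34 × 20.4) / (0 × 13.6), which is infinite. Referral route separates the outcome completely among cases, and neither covariates nor a random effect for the referring survivor can restore the missing variation. If controls must be eligible too, the outcome is constant and there is nothing to model.

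**3. The t test, if it uses these cases.** Assume that both routes bring in the same population, so the true difference is zero. The documents give no SD, so assume log-normal scores with log-SD σ from 0.7 to 1.3. Let p be the eligible share among controls within the matched age range, where eligibility depends on the score alone, and let a be the standard normal quantile at 1 − p. Then

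mean in cases / mean in controls = Φ(σ − a) / p.

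For p = 0.40, a = 0.253. At σ = 0.7 the ratio is Φ(0.447) / 0.40 = 1.68, and at σ = 1.3 it is Φ(1.047) / 0.40 = 2.13.

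Simulated two-sample t tests with 34 per group count how often cases are declared higher (nominal 2.5% in that direction):

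| Controls eligible | Ratio of means | Cases falsely declared higher |
|---|---|---|
| 40% | 1.68 to 2.13 | 65-92% |
| 60% | 1.38 to 1.57 | 27-55% |
| 80% | 1.17 to 1.23 | 8-16% |

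In each row the smaller log-SD gives the smaller ratio and the higher false-positive rate. The size is held at 34 throughout to isolate the effect of control eligibility. Larger groups make the error worse: with 78 per group and 60% of controls eligible it is 89% at log-SD 0.6 and 63% at 1.0. Clustering by referring survivor is not modelled.

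**4. With one entry rule for both groups.** In simulations under no true difference (log-SD 0.6 to 1.2, 40% eligible), the two-sided error is 4.1-5.4% for all referred against all program referrals, and 4.1-5.5% for eligible against eligible. The bias comes from the unequal entry rule.

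**The case against.** The strongest reply is that the t-test sentence itself names cohort 2, and the abstract and Table 1 agree. Three statements point to the whole referred group and one to eligible cases. If all of cohort 2 is compared, the truncation disappears. This stands, and it makes the t-test bias conditional. It does not help the case definition, which then contradicts the analysis or has no use.

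A second reply concerns the 40%. It describes program referrals before matching. Controls matched by age to cases aged 55 to 74 lose everyone ineligible on age alone, so their eligible share is probably above 40%. The documents do not give it. This also stands, and is why a range is shown.

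A reader might infer that the comparison favours survivor referral by construction, or that controls are known to be 40% eligible. The text supports neither. The bias needs the eligible-cases reading together with controls not all eligible. Under a mixed reading, with all adults in cohort 2 against controls matched to cases aged 55 to 74, the age difference would tend to work against survivor referral.

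Finally, the primary outcome in Table 1 is the mean risk in the referred population. It can be reported without controls and is not affected. The damage is confined to the objective 2 comparison in a study that the Discussion calls a pilot.

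**Conclusion.** The point holds as an internal contradiction over who enters the objective 2 comparison.

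- **Certain, with no distributional assumption:** with the case definition as written, the odds ratio for eligibility by referral route cannot be estimated, whichever way the controls are read. The definition also conflicts with the t-test sentence, the abstract, Table 1 and the calculation behind 194.
- **Conditional:** if the t test uses the eligible cases against controls not restricted to eligible people, false superiority ranges from about 65-92% when 40% of controls are eligible down to 8-16% when 80% are. This rests on log-normal scores, log-SD 0.7 to 1.3, 34 per group and no clustering. The bias vanishes only if all controls are eligible or all of cohort 2 is used.

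The definition should be corrected before analysis, because it makes one stated analysis impossible and leaves another open to serious bias.

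**What to change.** 1. Delete the case definition.
2. Compare all cohort 2 participants who have a PLCOm2012 score with program referrals selected regardless of eligibility.
3. Use eligibility only as the yes/no outcome of the logistic model. The 40% against 60% sample size already assumes this.
4. Keep the 1:1 age matching but apply it to all cohort 2 participants. Limit both groups to the age range in which matches exist, and describe unmatched participants separately.
5. If a comparison of eligible with eligible people is wanted, keep it as a secondary analysis. It is a valid test of mean scores but answers a narrower question than objective 2.

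**Cost:** revised analysis wording, and a control extract that includes ineligible program referrals. No new participants need to be enrolled. Cohort 2 members outside the matched age range leave the comparison.
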